### Pre-determined outcomes and sample size calculations

During the process of applying for funding for this research, the authors were required to specify a threshold for demonstrating “proof-of-concept” to the funding agency, Grand Challenges Canada (GCC) [29]. (Under GCC’s funding model, projects that demonstrate proof-of-concept may be eligible for expansion and longer-term funding). The authors and the funding agency agreed in advance on the outcomes and the minimum relative change in those outcomes that would be considered sufficient evidence to demonstrate that the intervention seems promising, i.e., demonstrates proof-of-concept:

A 10% increase in the proportion of participants who can identify at least one harmful consequence of child marriage for girls’ health, education, and/or economic opportunitiesA 20% increase in the proportion of participants who know that marriage before the age of 18 is illegal in Oyo State, Nigeria (where Ibadan is located)A 10% reduction in the proportion of participants who believe that the ideal age for girls to marry is younger than 18A 10% reduction in the proportion of participants who would support the marriage of girls in their families before the age of 18.

These pre-determined outcomes and the specified minimum change in those outcomes guided our sample size calculations. We want to be sure that we have sufficient statistical power to detect the effect sizes described above with a high degree of precision and, ideally, to detect even smaller effects. Assuming that 20% of persons surveyed at baseline already have the outcome of interest, we estimate that with a sample of 1600 persons, 50% of whom will be assigned to the treatment group (i.e., living in Ibadan), we can detect a minimum change of five percentage points in each outcome with 80% power at an alpha level of 0.05 [30].

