### Limitations

Funding for this study has been provided for a one-year period, which severely limits the timeframe for this intervention. The radio dramas will air for a period of three months. Earlier educational interventions that had a positive effect on gender equitable attitudes ran for more than two years [12, 13]. The limited timeframe to evaluate the intervention means that we cannot estimate its effect on actual behaviours like the incidence of child marriage. Instead, we will measure support for those behaviours, which may be a precursor to them. Our intervention may not be able to bring about a measurable change in attitudes over such a short period. However, we have powered our study to be able to detect relatively small effects, which would still be interesting for two reasons. First, if our short-term intervention results in small changes in the outcomes of interest, it is plausible that a longer-term intervention would result in stronger effects. Second, even a small effect from such a short-term and cost-effective intervention may be worth fielding more broadly among populations with high rates of child marriage.

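### At the assumed 20% baseline, the 10% and 20% relative proof-of-concept thresholds are 2 and 4 percentage points, below the 5-point minimum change the sample is sized to detect

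*Protocol article*

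**What the plan says.** All of the relevant figures are in the protocol article.

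- **Thresholds** (Pre-determined outcomes and sample size calculations). The authors and the funder agreed on "the minimum relative change in those outcomes that would be considered sufficient evidence to demonstrate that the intervention seems promising". The thresholds are a 10% increase in those who can name a harm, a 20% increase in those who know the legal position, a 10% reduction in those whose ideal age for girls is under 18, and a 10% reduction in those who would support such a marriage in their own family.
- **Aim** (same section). The thresholds are said to have guided the sample size. The authors want "sufficient statistical power to detect the effect sizes described above", and ideally power for smaller effects too.
- **Calculation** (same section). The inputs are "Assuming that 20% of persons surveyed at baseline already have the outcome of interest" and "with a sample of 1600 persons, 50% of whom will be assigned to the treatment group". The conclusion is that "we can detect a minimum change of five percentage points in each outcome with 80% power at an alpha level of 0.05".
- **Limitations.** The article later says that "we have powered our study to be able to detect relatively small effects".

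The Sampling procedure section gives 800 persons per city. The Statistical analyses section takes the city-by-time interaction as the treatment effect, with the same people interviewed twice.

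**The concern.** The thresholds are stated on a relative scale and the detectable change on an absolute scale. Once both are on one scale, at the baseline the authors chose, the detectable change exceeds all four thresholds. The aim and the calculation, which follow directly on each other, therefore do not agree.

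The thresholds matter because the article ties proof-of-concept to possible expansion and longer-term funding. If the intervention does just what was agreed as promising, the study would more often than not return a non-significant result for a 10% threshold, and would fall well short of 80% power for the 20% threshold. A reader who relied on the stated aim and on the Limitations could then take a null result as evidence against an effect that the study was unlikely to detect.

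**Working it through.** **Inputs**, all from the sample size section: baseline 20% for every outcome; 1600 persons, half in each city; power 80%; alpha 0.05; thresholds of 10% and 20%, relative. Two-sided testing is my assumption, since sidedness is not stated.

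**Step 1. One scale.**
- 10% threshold: 0.10 × 20% = 2 points (20% to 22%, or 20% to 18%).
- 20% threshold: 0.20 × 20% = 4 points (20% to 24%).
- Stated detectable change: 5 / 20 = 25% relative. This is 2.5 times the 10% threshold and 1.25 times the 20% threshold.

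The mismatch is already established here and needs no power formula.

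**Step 2. The plan's own figure.** For two proportions with n = 800 per city and p̄ the mean of p1 and p2,

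power = Φ{[|p1 − p2| − 1.96·√(2p̄(1−p̄)/n)] / √([p1(1−p1) + p2(1−p2)]/n)}.

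- 20% to 25%: (0.05 − 1.96 × 0.02088) / 0.02084 = 0.44, power 67%.
- 20% to 15%: (0.05 − 1.96 × 0.01900) / 0.01896 = 0.67, power 75%.

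On this formula the change detectable with 80% power is 5.9 points upward or 5.3 downward. Five points is matched only with choices the article does not state: a one-sided test using the baseline variance alone (4.97 points), or a difference-in-differences with a within-person correlation of about 0.58 to 0.62. Because neither is ruled out, I do not count the 5-point figure as an error. The threshold powers are given both ways.

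**Step 3. Power at the thresholds, accepting 5 points at 80% power.**
- Implied standard error: 5 / (1.960 + 0.842) = 1.785 points.
- 2 points: Φ(2/1.785 − 1.96) = Φ(−0.84) = 20%.
- 4 points: Φ(4/1.785 − 1.96) = Φ(0.28) = 61%.
- Total N for 80% power: 1600 × (5/2)² = 10,000 and 1600 × (5/4)² = 2,500.

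**Step 4. Power at the thresholds, direct calculation with 800 per city.**

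| Change | Two-sided power | One-sided power | N per city for 80% (two-sided) |
|---|---|---|---|
| 20% to 22% | 16% | 25% | 6,510 |
| 20% to 18% | 17% | 27% | 6,039 |
| 20% to 24% | 49% | 61% | 1,683 |

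**Step 5. What would change the answer.**
- *Baseline.* In the direct two-sided comparison, a 10% relative change reaches 80% power only from a baseline of about 65% (increase) or 67% (reduction), and a 20% increase only from about 34%.
- *Repeated measures.* For a difference-in-differences with within-person correlation ρ, the variance is the sum over the two cities of [a(1−a) + b(1−b) − 2ρ√(a(1−a)b(1−b))]/n, where a and b are the baseline and follow-up proportions. Power of 80% then needs ρ of about 0.94 for 2 points and 0.76 for 4 points. No correlation is stated.
- *Clustering.* An assumed design effect of 1.5 to 2 lowers the direct powers to about 12-10% (20% to 22%) and 35-28% (20% to 24%). Attrition would lower them further.

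**The case against.** Four points can be made for the authors.

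1. **The power statement is an aim.** This stands. The sentence about the thresholds says what the authors want, and the only sensitivity they report as achieved is 5 points at a 20% baseline, stated openly. A reader might infer that the article falsely claims power for the thresholds. The text does not go that far: the calculation fails to deliver an aim. The Limitations sentence is worded as something done, but it speaks of relatively small effects and does not mention the thresholds.

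2. **The thresholds may have been meant as percentage points.** The list items themselves say only 10% and 20%. If 10 and 20 points were meant, 5 points is smaller than either, and the hope of detecting smaller effects makes sense. Against this, the introducing sentence calls them "the minimum relative change in those outcomes that would be considered sufficient evidence". The relative reading is what is written, but the other cannot be excluded. On either reading something in the section needs correcting.

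3. **Actual baselines may be higher, and repeated interviews gain precision.** Both are true in principle, and step 5 shows how much of either would be needed. The article nevertheless applies 20% to every outcome and states no correlation.

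4. **Proof-of-concept is not tied to significance.** This also stands. The article defines it by a minimum change and does not say that a significant test is required. A reader might infer that low power means the funder's criterion cannot be met, and the text does not support that. The consequence concerns how a non-significant result is read. The Limitations do warn that no measurable change may appear, but they attribute this to the short broadcast period and not to limited power.

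**Conclusion.** The point holds in this form: taking the thresholds as relative, as written, and the baseline as 20%, as assumed, the sample size does not deliver the stated aim of 80% power for effects of threshold size, still less for smaller ones. The Limitations statement about small effects is not supported for effects of that size.

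The shortfall is large for the three 10% thresholds (power about 16-20%) and moderate for the 20% threshold (about 49-61%). The upper figure in each range accepts the 5-point statement; the lower comes from the direct calculation. Both assume a two-sided 0.05 test and no clustering or attrition. The comparison of 2 and 4 points with 5 depends on none of these assumptions.

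Which element is wrong, the threshold scale or the power reasoning, cannot be settled from the article.

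**What to change.** First, reconcile the scale: confirm with the funder agreement whether the four thresholds are relative or percentage-point changes.

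**If relative:**
- Put each threshold in percentage points beside its detectable difference, recomputed with the intended test, its sidedness and the observed baseline proportions from the survey already under way.
- State that at a 20% baseline the study does not have 80% power for the 10% or the 20% threshold.
- Qualify the Limitations sentence by giving the size of effect the study can detect.
- Add that a non-significant result does not rule out an effect of threshold size.

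**If percentage points:** correct the word *relative* in the sentence that introduces the thresholds. The stated aim and the 5-point figure are then consistent with each other.

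The sample should not be enlarged: recruitment began in February 2023, and the 12,000 to 13,000 persons that the direct calculation implies for a 2-point change are out of proportion to the planned 1600. The change is to wording plus a short recalculation. The only cost is a less favourable statement of sensitivity.

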### Sampling procedure

Participants will be recruited through a multi-stage cluster sampling approach. In the first stage, enumeration areas (called settlements) within known Hausa neighbourhoods (wards) of Ibadan and Akure will be randomly selected from existing lists developed by health care centres in those wards. In the second stage, houses within selected enumeration areas will be randomly selected using lists obtained from the Nigerian National Population Commission (NPC). Multiple households often reside within the same residential building in these cities. Every household in a selected building that includes at least one eligible participant will be invited to participate. If households include more than one eligible participant, one individual will be randomly selected. If buildings selected from the NPC lists are abandoned or not in residential use at the time of the survey, new buildings will be randomly selected to replace them. Using this sampling approach, we will randomly select a total of 1600 persons to participate: 800 in Ibadan and 800 in Akure.

### Inclusion criteria

Eligible participants must be 40 years of age or older, be of Hausa ethnicity, reside in one of the selected neighbourhoods in Ibadan or Akure, and have no intention of moving away from the neighbourhood within six months following the baseline survey. Eligible persons must also be willing to share their contact information so that they can be reached for a follow-up interview.

### Variables to be measured

The baseline survey will record demographic characteristics of participants to determine how exchangeable intervention and control samples are prior to the intervention. The baseline and follow-up surveys will also collect information on participants’ knowledge and perceptions of child marriage. These questions will be worded identically on both surveys to facilitate measurement of change following the intervention. The baseline survey questionnaire is included in the appendix. We have several outcomes of interest. Those necessary for demonstrating proof-of-concept to the funding agency are:

The proportion of persons in Ibadan who report having listened to at least one radio drama during the intervention period. This will be assessed using the question, “Did you hear stories about child marriage broadcast on [radio stations] in the past few months?”The proportion of persons who are aware that marrying before the age of 18 is illegal in Oyo and Ondo state, where Ibadan and Akure are respectively located. This will be measured by correct responses to the question, “According to the law, what is the youngest age at which a person can get married in [Oyo or Ondo] State?”The proportion of persons who believe that the ideal age for girls to marry is younger than 18 years. This will be measured by responses to the question, “In your opinion, what is the ideal age for a girl to get married?”The proportion of persons who would support the marriage of girls in their families before the age of 18, measured based on responses to the question, “Would you support the marriage of a girl in your family before she turned 18?”The proportion of persons who correctly identify at least one harmful consequence of child marriage, as indicated through pre-defined responses to the question, “What are the possible harms to a girl if she marries before she turns 18?”

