We have budgeted to air the radio dramas three times per week on three separate Hausa-language stations based in Ibadan over a three-month period in 2023. Incentives will be provided to promote listenership. At the end of each radio drama, listeners who correctly respond to a question about the content will be entered into a drawing for pre-paid mobile phone credit. Two local Hausa celebrities will also be hired to participate in the dramas to increase their appeal to a broad audience. We verified that the broadcast range of these stations does not extend to Akure, the control city, but some of these stations allow listeners to tune into their programming online. This means that some degree of spill over of the intervention is possible. However, our target population includes persons aged 40 and older, whom we believe are unlikely to seek out online radio broadcasts, and we will look for evidence of spill over in Akure during the follow-up survey.

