### Research design

We will measure the impact of our intervention using a controlled, pre-post design. A baseline survey will be conducted in both cities prior to the intervention to measure knowledge and perceptions of child marriage, including the ideal age for marriage among boys and girls, the perceived benefits and harms of marrying early, and knowledge of the minimum age for marriage specified by law. The baseline questionnaire was written in English and will be translated into Hausa and Yoruba, the primary languages spoken among Hausa persons living in Ibadan and Akure.

The radio dramas will be broadcast in Ibadan for a period of three months. Afterward, we will follow up with the same individuals who participated in the baseline survey in both cities and ask them to complete a second interview. The follow-up interview will measure coverage of the intervention, i.e., whether participants heard the radio dramas, and will ask many of the same questions as the baseline interview so that we can measure changes in these outcomes over time.

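### The question that measures reach does not identify the study's dramas or their airing period, so reach in Ibadan can be misstated and a yes in Akure cannot establish spill-over

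*Protocol article*

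**What the plan says.** In the protocol article, Variables to be measured lists five outcomes as needed for proof-of-concept. The first is reach: "The proportion of persons in Ibadan who report having listened to at least one radio drama during the intervention period". The same entry fixes the instrument, a single question: "Did you hear stories about child marriage broadcast on [radio stations] in the past few months". Reach is also the first of the three aims under Research objectives, where it is stated for Ibadan.

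Under Intervention, the dramas are to air "three times per week on three separate Hausa-language stations based in Ibadan over a three-month period in 2023". Akure is outside the broadcast range, but "some of these stations allow listeners to tune into their programming online", so some spill-over is thought possible and "we will look for evidence of spill over in Akure during the follow-up survey".

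Under Research design, "we will follow up with the same individuals who participated in the baseline survey in both cities", and "The follow-up interview will measure coverage of the intervention, i.e., whether participants heard the radio dramas". The article does not say which item will be used to look for spill-over in Akure.

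**The concern.** The outcome and its question differ in two respects.

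- **Object.** The outcome is hearing a study drama. The question is about stories on child marriage in general on the named stations. A respondent who heard a different programme on the topic there can truthfully say yes.
- **Window.** The outcome refers to the intervention period. The question refers to an unspecified recent span of months, which can take in content aired before the dramas began.

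False recall is a further route. Participants will already have been interviewed about child marriage at baseline, so they know the topic when a yes/no question on it is put to them.

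Reach is the first objective, and it also guides how the effect results are read. If attitudes do not move, a high reach figure points to a message that failed and a low one to a message that was not heard. An exposure item that counts non-listeners as listeners blurs that distinction, most of all when true reach is low.

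**Working it through.** The article gives no expected reach, reach threshold, false-yes rate or recall rate, so there is no stated figure to reproduce. The rates below are assumptions chosen to show the range.

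**Reach in Ibadan.** Let r be true reach, s the share of true listeners who say yes, and f the share of non-listeners who say yes. Then

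reported reach = s × r + f × (1 − r).

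Example: r = 40%, s = 80%, f = 10% gives 0.80 × 0.40 + 0.10 × 0.60 = 0.32 + 0.06 = 38%.

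| True reach r | Recall s | f = 5% | f = 10% | f = 20% | f = 30% |
|---|---|---|---|---|---|
| 20% | 100% | 24% | 28% | 36% | 44% |
| 20% | 80% | 20% | 24% | 32% | 40% |
| 40% | 100% | 43% | 46% | 52% | 58% |
| 40% | 80% | 35% | 38% | 44% | 50% |
| 80% | 100% | 81% | 82% | 84% | 86% |
| 80% | 80% | 65% | 66% | 68% | 70% |

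The net error is upward when f exceeds (1 − s) × r / (1 − r). With s = 80% the break-even false-yes rate is:

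- r = 10%: 0.02 / 0.90 = 2.2%
- r = 20%: 0.04 / 0.80 = 5%
- r = 40%: 0.08 / 0.60 = 13.3%
- r = 80%: 0.16 / 0.20 = 80%

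So at low true reach a small false-yes rate is enough to inflate the figure, while at high reach under-recall dominates.

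**The same item in Akure.** Let e be the true exposed share. With perfect recall the yes-rate is e + f × (1 − e). Assume e = 2%, since online listening is the only spill-over route the article names and it regards that as unlikely in this age group.

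- f = 5%: 0.02 + 0.98 × 0.05 = 6.9%, of which 0.02 / 0.069 = 29% are real exposures.
- f = 30%: 0.02 + 0.98 × 0.30 = 31.4%, of which 0.02 / 0.314 = 6% are real.

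The yes-rate then bounds e from above. With imperfect recall it still does so provided false yeses outnumber missed listeners. At s = 80% and e = 2% that needs f of only 0.2 × 0.02 / 0.98 = 0.4%.

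**Precision of that bound.** The planned sample is "800 in Ibadan and 800 in Akure". With full follow-up and simple random sampling, the 95% half-width is 1.96 × √(p(1 − p)/800), which is 1.5 points at p = 5% and 2.8 points at p = 20%. The planned cluster sampling and any loss to follow-up would probably widen it.

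**The case against.** Several points on the other side are sound, and they limit what can be claimed.

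- A reader might infer that any radio story on child marriage counts. It does not: the question is tied to named stations, and the article does not say that those stations carry other programmes on the topic.
- A reader might infer that reach will be overstated. The documents do not show this. They give no false-yes rate, and under-recall works the other way, as the 80% recall rows at true reach of 40% (for f up to 10%) and of 80% show.
- A reader might fault the outcome for covering Ibadan only. Ibadan is the population of the first objective, so that is the matching measure.
- A reader might conclude that the spill-over check cannot be interpreted. Follow-up is planned in both cities, and a low Akure yes-rate would be informative as a bound.
- The follow-up questionnaire is not shown, the station names are still a placeholder, and the dramas were still being developed. Identifying items may be added.
- No stated decision can be shown to change. Pre-determined outcomes and sample size calculations sets no threshold for reach, and reach does not enter the model under Statistical analyses.

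The mismatch itself remains. The article does not leave the wording open: it assigns this outcome to this one question, and the question asks about something broader than the outcome. That the outcome is expressly self-reported does not answer this, because the self-report is about a different object and window.

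**Conclusion.** The concern holds in a limited form. As written, the question can misclassify exposure, so the reach figure in Ibadan can be wrong in either direction. Upward error is the more plausible when true reach is low. The size cannot be derived from the documents. Under assumed false-yes rates of 5% to 30% and recall of 80% to 100%, true reach of 20% would be reported as 20% to 44%, 40% as 35% to 58%, and 80% as 65% to 86%. If the same item is used in Akure, its yes-rate is a non-specific upper bound on spill-over and cannot show that spill-over occurred. The four knowledge and attitude outcomes and their analysis are unaffected. What is at stake is the first objective and the reading of a null effect.

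**What to change.** In the follow-up questionnaire:

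1. Name the series by title and lead characters, and state the airing months.
2. Add one content-recognition item that is hard to answer without having heard a drama, and one decoy title that was never broadcast.
3. Ask all of these identically in both cities, and say so in the protocol.

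In reporting, give Ibadan reach twice: as claimed, and as confirmed by correct content recognition. Present the Ibadan decoy yes-rate beside them as the gauge of false recall. Count spill-over in Akure only when content is correctly recognised. Do not subtract the Akure yes-rate from Ibadan reach. The stations do not broadcast in Akure, so that rate does not estimate false yeses arising in Ibadan from other programmes, and it may contain real spill-over.

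The cost is two or three short items, and the reported reach may be lower. True listeners who cannot recall the content would fail confirmation, which is why both figures are needed. On the timeline in the article, airing was still ahead and follow-up comes after it, so the change could be made in time. The rule that questions be worded identically at baseline and follow-up concerns knowledge and perceptions, so changing the exposure item does not disturb the pre-post comparison.
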